## Abstract

Chronic migraine is a debilitating headache disorder that is associated with excessive analgesic use. As the long-term use of analgesics could cause additional headaches due to medication overuse, there is a need to probe efficient nonprophylactic alternatives and migraineurs’ long-term adherence to such possible treatments. This protocol investigates the integration of neurofeedback and mindfulness which are the two common nonpharmacological therapies for migraines. We offer the use of portable EEG headbands for easy home-based data collection and consistent data access from researchers. In order to evaluate the efficacy of this recommended intervention, this is a protocol for a randomized control trial with a waitlisted group and an intervention group consisting of a daily attention task. The protocol presents important criteria which should be checked for consistency in longitudinal data collection from adults with chronic migraine.

## Introduction

1

Migraine is a complex neurological disorder that is comorbid with psychiatric disorders [1,2] or cognitive dysfunction [3,4]. Migraine is the first category of primary headache disorders in the third edition of the International Classification of Headache Disorders [5] and is described based on specific headache characteristics that define subtypes causing mild to severe levels of disability that usually require prophylactic and/or non-prophylactic treatments [6]. Any form of migraine with headaches less than 15 times per month is considered as “episodic migraine”, but if headaches occur on 15 or more days per month for a duration of more than 3 months with at least 8 days/month having features of migraine, then the headaches are categorized as “chronic migraine” which are a bigger cause of disability [5].

Chronic migraine is a form of primary headache disorder, but most of the symptoms overlap with “medication-overuse headache” (MOH), a term generally used for the caused increase in frequency of primary headaches attributed to frequent use of acute or symptomatic medication [7]. Given that long-term pharmacological treatments for migraine could expose the individuals to side effects such as more increased headaches as a function of MOH, it is important to explore the efficacy of non-pharmacological treatments more seriously.

Currently there are many nonpharmacological approaches which are being studied for migraine management, most of which still need to be further explored in terms of their optimization [8]. For example, transcranial magnetic stimulation (TMS) is a procedure during which a magnetic coil is used to influence the electrical activities of the cortex, so the frequency of migraine attacks is reduced, but the available literature review does not support whether this treatment efficiently reduces pain severity or not [9]. At the same time, systematic reviews on other forms of treatments do not provide enough evidence for a decrease in migraine intensity followed by cognitive-behavioural therapy [10] or changes in migraine frequency and medication use followed by acceptance and commitment therapy [11]. Regarding this, the available gap urges more investigation of approaches that not only reduce the frequency and intensity of migraines, but they can also improve individuals’ self-efficacy to manage their headaches with less medical alternatives.

Two other well-known non-pharmacological alternatives for migraine headaches are neurofeedback and mindfulness meditation [12]. Neurofeedback therapy is a non-invasive technique of recording electrical activities of the cortex through EEG and presenting this as feedback to the user in real time while the participant is doing a specific task. Neurofeedback is a subcategory of biofeedback therapy as it engages participants to influence their cortical activities based on the display representing their brainwave activities [13]. At the same time, mindfulness meditation is an evidence-based intervention with practices that specifically concentrate on health improvement. Mindfulness includes states or traits that assist a relaxed non-reactive observation of the mind and bodily functions [14]. Mindfulness technique modifies how one attends to the internal and external factors; the efficacy of this attentional adjustment is found to be beyond a placebo effect or a sham effect [15]. However, there are still questions about the complexity of mindfulness and its relation to the other attention-based practices [17]. A recent investigation has showed that sham mindfulness with some focused-attention techniques might result in improvements in pain threshold similar to mindfulness; nevertheless, the impact on the quality of observing the pain and evaluating its unpleasantness is still significantly greater as a function of mindfulness. Additionally, Davies et al. [16] recommend regular mindfulness practice as a helpful technique for migraine management but they suggest studies that evaluate its efficacy compared to other novel controlled interventions.

In general, the past decade has brought about new research into mindfulness-based treatments as a promising non-pharmacological alternative for migraine management showing that mindfulness could decrease both migraine frequency and intensity [[17], [18], [19], [20], [21]]. Nonetheless, while neurofeedback is a convenient technique for tangible and concrete monitoring of physiological changes throughout a migraine treatment, the studies of neurofeedback and migraine are still few in numbers and most of them have been applied on pediatric populations or in lab-based contexts [[22], [23], [24], [25]]. Studies on either neurofeedback or mindfulness meditation have varied study designs and methodologies yet randomized controlled trials (RCTs) are considered the most appropriate study design for investigating the efficacy of treatments. Yet, more information is needed on how to implement a consistent long-term study of these techniques in the migraine population.

Since it is hard to fully discover if an individual is doing the mindfulness-based practices correctly at a home-based context, real-time EEG feedback could help the participants to learn how to modify their bodily postures and their practices for an optimized practice. So far, no study has ever investigated the efficacy of portable EEG headbands in migraine management and there is a need to see if such emerging technologies are promising or not.

In terms of exploring a new non-pharmacological alternative, the following notes should be critically considered: 1. Cognitive and psychiatric symptoms are associated with migraine headaches [26]; this suggests that alternative treatments should attend to the multifaceted need of adults with chronic migraine for something that improves their quality of life and mental health, not only to cope with pain during an attack, but also to prevent from further attacks through modifying stressors. 2. Since adults with chronic migraine have a higher chance of MOH as the function of frequent intake of analgesics to avoid pain, we need to explore how the suggested alternatives could improve headache sufferers’ pain tolerance and ability to withhold or decrease the overuse of medicine. 3. Most importantly, we need to evaluate practice adherence and feasibility of the alternative with regards to the amount of commitment that participants would have towards the recommended treatment. Both adherence and feasibility are important factors to consider when investigating a non-pharmacological treatment in order to ensure its long-term effectiveness for chronic conditions.

We present our RCT protocol on the efficacy of neurofeedback mindfulness meditation for adults with chronic migraine. In this protocol, we describe a portable EEG headband (MUSE), we address the possible challenges regarding the project launch, data collection, and daily follow up with the participants. The current RCT protocol presents a valuable investigation of a non-pharmacological treatment for chronic migraine for the following reasons: 1. We have taken a novel approach by integrating two common non-pharmacological approaches for migraine i.e., neurofeedback and mindfulness meditation. 2. We introduce a novel controlled intervention that will be discussed in further details. 3. We offer an innovative longitudinal design with direct and consistent follow ups for the whole duration of the study. 4. This study focuses on self-guided mindfulness for naïve meditators who never receive formal training for their practices.

Both mindfulness and neurofeedback techniques have “attentional adjustment” as a key point in common; something that is found to be impaired in migraine headache [[27], [28], [29]]. No previous study has investigated whether the joint techniques could be different from a similar controlled intervention. While it is speculated that neurofeedback mindfulness provides an internal source for the subjects to attend to (e.g., their breath, and their stream of thought) and actively engages them to modulate their cognitive and behavioural responses, our controlled group will also have a level of attentional engagement with their given stimuli. Comparing these two interventions will reveal if migraine management requires a mindfulness routine engagement or if simple attentional adjustments could be sufficient. At the same time, previous literature is suggestive of an interaction between the expectancy and belief in treatments with the reports of improvements by headache sufferers [30]. Hence, it is an important to check whether there is an association between how people benefit from interventions based on their belief in the recommended treatments. Regarding this, in our RCT protocol participants will also be assessed on their belief in the given interventions and how it might impact dependence on medicine intake.

In this longitudinal RCT, we will use a portable Canadian-based EEG headband called MUSE by InteraXon. This headband facilitates data collection in a more convenient way compared to lab-based investigations. Because they can take it home, this headband enables participants to learn about their cortical activities more frequently than when they are asked to come in and wear EEG caps in a lab-based setting. There is a rising interest in the use of wearable interactive devices for telehealth and innovative healthcare support, facilitating a patient-centered health provision and telemonitoring [31]. As a validated portable EEG device [32], MUSE is designed to enable participants with a report of their attention based on their brainwaves during different relaxation techniques; such devices are found helpful with moment-to-moment reports of the electrical activities in different conditions [31]. This device is known as a low-cost EEG device (less than 500 CAD) [31,33] and enables a more convenient remote access to participants’ practices via a suggested platform, called MUSE Connect, where the practice history of the individuals is displayed.

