## Hypotheses

2

The main goal of the presented RCT protocol is to evaluate how 8 weeks of neurofeedback mindfulness using a wearable EEG headband could moderate headache experience (including frequency and intensity), headache management self-efficacy, psychiatric symptoms (i.e., anxiety and depression) and dependence on analgesics for adults with chronic migraine who are also identified as naïve meditators. The specific measures are described in more detail below. The following hypotheses are tested in this RCT.1.After completing the intervention, neurofeedback mindfulness will improve headache experience across time via:a.Decreased migraine disabilityb.Decreased migraine intensityc.Increased headache management self-efficacya.Decreased anxietyb.Decreased depressionc.Decreased level of dependence on medication.2.Participants in the neurofeedback mindfulness group will have significantly lower scores in migraine disability and intensity, and significantly higher scores in headache management self-efficacy when compared to the attention control group and the waitlisted group.3.Participants in the neurofeedback mindfulness group will have lower anxiety and lower depression scores when compared to the attention control group and the waitlisted group.4.Neurofeedback mindfulness participants will have a significant decrease in the level of dependence on medication, compared to those in the controlled intervention and waitlisted groups.5.There will be no impact of participants' belief in meditation on any of the measured criteria (e.g., migraine characteristics and psychiatric symptoms) across time.

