### The assigned tasks

3.6

In this study, the participants will be randomly allocated in three groups of neurofeedback-mindfulness, the controlled intervention, and waitlisted groups. The allocation will be done using stratified randomization to ensure equal distribution (1:1:1) among groups.1.The neurofeedback mindfulness groupThis group is asked to sit comfortably in a quiet area and do one of ten beginner self-guided mindfulness sessions on mind-body scanning techniques from within the MUSE app. Each session includes a brief explanation for 2–3 min before the practice. The participants repeat the same sessions throughout the intervention.1.Introduction to mindfulness: a brief review of mindfulness as a nonjudgmental observation of body and mind.2.Training a puppy: how to monitor emotions and control reactions to different states of mind.3.Sensation of breath: the importance of mindful breathing techniques.4.Counting breaths: how to inhale and exhale properly.5.Sitting comfortably: how to modify positions for mindfulness practices.6.Finding your soundscapes: monitoring the states of mind and how they are associated with the given neurofeedback sounds.7.Dealing with distraction: describing nonreactivity and acceptance of different states of mind.8.Working with discomfort: how to mindfully adjust the states of mind in unfavourable conditions.9.Lowering the bar: Moderating expectations from practices and accept the present state of mind without changing it.10.Bridging to daily life: bringing attention to how the state of acceptance could be conceptualized in everyday routines.

Once the participants start their practices, they receive sounds for their real-time brain activities: thunderstorm for an active state, ocean waves for a neutral state, and birds chirping for a relaxed state. For each 5 s of consistent relaxed state, the participants are reinforced with points.2.The attention control group

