### Participants

3.9

According to A priori G*power software calculation for this study considering both between-subject and within-subject effects, a sample size of 66 is expected to detect significance level of 0.05 with 95 % power through our planned statistical analysis test, i.e., Repeated Measures ANOVA. We aim to look at the effect of time by comparing the baseline with mid-/post intervention reports of the participants for each of the six measurements independently; moreover, we will compare the interaction of time*groups separately for each of our six scales. We will initially allocate 180 participants; yet with reference to the previous studies [22], we could expect up to 50 % of attrition. After applying inclusion and exclusion criteria, participants will be selected for either the meditation, the control, or the waitlisted group. We speculate a higher number of attritions in the meditation and control groups regarding the complexity of the given tasks as compared to the waitlisted group. Fig. 3 provides a flowchart for the number of expected participants at each stage of the study.

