### Statistical methods

3.12

This protocol is primarily based on comparing the baseline information of the participants with their information on Weeks 4 & 8 of their intervention. With regards to this, we will use Repeated Measures ANOVA for comparing the effect of time on the participants' changes in chronic headache characteristics, psychiatric symptoms, and medicine intake. Additionally, we will compare the interaction effect of time* groups to discover which of the three groups would show most significant changes across time as measured independently for each of the study's scales.

For each of the task-based groups, we will explore the total missed days and attrition at each of the task groups to discover the level of adherence for the two task-based groups. The diaries will also be compared across time to discover how participants manage their headaches via different alternatives and whether there is a change in their trend of headache medicine intake.

Finally, the EEG data analysis will be applied for within-subject and between subject comparisons to determine whether there is a change in adults with chronic migraine's peak alpha frequency over time and during their headache experiences as a function of their practices.

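### The Introduction says the mindfulness-attention comparison will show whether simple attention could be sufficient, but the planned superiority test cannot support that answer

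*Protocol article*

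**What the plan says.** The Introduction gives this reason for including the attention arm: "Comparing these two interventions will reveal if migraine management requires a mindfulness routine engagement or if simple attentional adjustments could be sufficient".

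The other relevant statements in the protocol article are these:

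- **Hypotheses (section 2).** Hypotheses 2 to 4 all predict that mindfulness does better than both the attention control and the waitlist. Hypothesis 2, for example, says the mindfulness group "will have significantly lower scores in migraine disability and intensity". No hypothesis states equivalence or non-inferiority, and none compares attention with waitlist.
- **Statistical methods (section 3.12).** The between-group analysis is the interaction term: "we will compare the interaction effect of time* groups to discover which of the three groups would show most significant changes across time", done separately for each scale.
- **Participants (section 3.9).** "a sample size of 66 is expected to detect significance level of 0.05 with 95 % power through our planned statistical analysis test". No effect size or between-visit correlation is given. The same section says "We will initially allocate 180 participants", expects up to 50% attrition, and expects more of it in the two task arms than in the waitlist.
- **The assigned tasks (section 3.6).** Allocation is by "stratified randomization to ensure equal distribution (1:1:1) among groups".

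No margin and no confidence-interval rule for the mindfulness-attention comparison appears in the article.

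**The concern.** The Introduction offers two possible answers from one comparison: mindfulness is required, or simple attention could be enough. The planned test serves only the first. Rejecting the null supports the statement that mindfulness adds something. The article provides no route to the second answer except failure to reject, and failing to reject does not show that two treatments are close.

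The sentence also leaves out a condition. For attention to be sufficient it has to help at all, which means doing better than the waitlist. Two tasks that both do nothing would also fail to differ.

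What is at stake is how a null result is interpreted. If mindfulness has a moderate advantage that the trial misses, the published conclusion could be that checking email, news or social media for ten minutes serves as well.

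**Working it through.** **The plan's own figure.** Section 3.9 states N = 66 for 95% power at 0.05. It cannot be reproduced from the article, because the effect size f and the correlation are not given. Several settings come out at 66. With G*Power's convention λ = f²·N·m/(1−ρ), three groups, m = 3 visits and ρ = 0.5, a within-subject time effect of f = 0.20 gives λ = 0.04 × 66 × 3 / 0.5 = 15.84 and power 95.0%. A time-by-group effect of f = 0.25 with only two visits also needs 66. So the stated 95% cannot be taken as the power of the mindfulness-attention contrast.

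**Inputs for the illustration**

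- Completers per arm: 66/3 = 22 (section 3.9 with 1:1:1 allocation), and 180 × 0.5 / 3 = 30 (180 allocated, 50% attrition, equal loss across arms).
- Two-sided 0.05 (the article gives 0.05 only).
- Assumed: SD 1 at each visit, equal correlation r between visits of 0.5, 0.7 or 0.8, and a true mindfulness advantage of 0.5 SD in change from baseline to Week 8.

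**Chance of a non-significant difference**

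SD of change = √(2(1−r)). Standardised difference d = 0.5/√(2(1−r)). Noncentrality = d·√(n/2), with 2n−2 degrees of freedom. The miss rate is the probability that |t| stays below its critical value.

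| r | SD of change | d | Miss rate, n = 22 (noncentrality) | Miss rate, n = 30 (noncentrality) |
|---|---|---|---|---|
| 0.5 | 1.000 | 0.500 | 63% (1.66) | 52% (1.94) |
| 0.7 | 0.775 | 0.645 | 45% (2.14) | 31% (2.50) |
| 0.8 | 0.632 | 0.791 | 27% (2.62) | 15% (3.06) |

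The time-by-group F test restricted to the two task arms gives similar or higher miss rates at r = 0.5 and 0.7. With the full effect present from Week 4 they are 63% and 42% at 22 per arm, and 51% and 28% at 30. With a linear build-up they are 71% and 55%, and 62% and 41%. With no attrition (60 per arm) the Week 8 change comparison still misses 22% at r = 0.5, but only 6% at r = 0.7.

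**What a confidence interval would show**

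Expected 95% half-width ≈ t·√(2(1−r))·√(2/n):

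- n = 22: 0.61 SD at r = 0.5 and 0.47 SD at r = 0.7.
- n = 30: 0.52 SD at r = 0.5 and 0.40 SD at r = 0.7.

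If the true difference is zero, a non-significant result also excludes a 0.5 SD mindfulness advantage in this share of cases (by simulation):

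- r = 0.5: 36% at 22 per arm, 48% at 30.
- r = 0.7: 56% at 22 per arm, 70% at 30.

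If the true advantage is 0.5 SD, the interval wrongly excludes it in only about 4-8% of the non-significant results over the same settings. Non-significance and exclusion of a margin are therefore different findings, and only the second bears on sufficiency.

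**The case against.** The strongest reply is that the protocol contains no rule turning p > 0.05 into sufficiency. The sentence is Introduction rationale and is hedged with 'could be'. The formal hypotheses are superiority hypotheses, and a superiority test suits them. This stands: a reader might infer that the trial will declare attention sufficient whenever the arms do not differ, but the document does not say so. What remains is that the sentence promises the comparison will reveal which answer holds, and the stated analysis cannot deliver one of them.

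The second reply is that the waitlist is not missing from the plan. It is one of the three groups in the interaction test, so an inert attention task could be recognised. This also stands. It would be tempting to say that if neither task works, sufficiency would be concluded about 95% of the time. That figure is only 1 − 0.05 and presupposes that the waitlist is ignored. If attention must also be significantly better than the waitlist, the combination occurs about 2% of the time when no arm has any effect. The residual point is that the sentence rests the conclusion on the two task arms alone.

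Third, the miss rates depend on a 0.5 SD effect and correlations that appear nowhere in the article, and they fall well below a half at r = 0.8. That is correct, so no single range can be stated as a property of this trial. Nor can it be said that a null result would usually fail to exclude 0.5 SD: at r = 0.7 it would exclude it more often than not if the true difference were zero.

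Finally, contrasts and intervals are often left to an analysis plan. That is true of the detail, but here the article itself states the inference.

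**Conclusion.** The point holds in a limited form. The Introduction offers a conclusion that the hypotheses and the 0.05 Repeated Measures ANOVA cannot support: the analysis can show added benefit of mindfulness, but a non-significant difference does not show that attention is enough. The reasoning needs no assumption about effect size. The size of the risk does: under the assumptions above, a real 0.5 SD advantage would go undetected in anything from about 15% to 63% of trials, depending on the correlation and on whether 22 or 30 per arm complete. If attrition is concentrated in the task arms, as section 3.9 expects, those arms could end below 30 each even with 90 completers overall. The superiority hypotheses and their test are not affected.

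**What to change.** - **Introduction:** reword the sentence to ask whether mindfulness adds benefit over the attention task.
- **Section 3.12:** for each scale, report the mindfulness-minus-attention and attention-minus-waitlist differences in change to Week 8 with 95% confidence intervals. State that a non-significant mindfulness-attention difference is inconclusive on its own.
- **If the sponsor wants to keep a sufficiency conclusion:** allow it only when the interval for mindfulness minus attention excludes a pre-stated, justified margin and attention is better than the waitlist. Whether 22-30 completers per arm can achieve this depends on the between-visit correlation. As a guide, on the Week 8 score without baseline adjustment, an illustrative 0.5 SD margin needs 63 evaluable per arm for 80% power at one-sided 0.025 with a true difference of zero.

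The cost is a change of wording and two contrasts from data already being collected, with no extra participants. The downside is that a null mindfulness-attention result has to be reported as inconclusive.
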